### Study aims and objectives

The primary aim of the project is to investigate the extent to which patient’s preferences for treatment influences a broad range of primary and secondary outcomes: panic symptom severity, agoraphobic avoidance, occupational status, sickness-related absences, subjective working ability, psychiatric comorbidity, panic and depression-related disability, and healthcare/medication utilization. A secondary aim is to compare outcomes for PCT, which is the form of CBT with the largest evidence base for PD, to PFPP, both of which are already delivered in routine care facilities in Sweden. A tertiary aim is to evaluate in a multivariate fashion, interactions between patient preference and other potential moderators of outcome (for example, gender, age, symptom severity, Axis I and II comorbidity, medication use, strength of the therapeutic alliance, and therapist effects). Finally we aim to evaluate putative mechanisms of change associated with each of the evaluated treatments (for example, cognitive and behavioral change, reflective capacity).

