While further comparative trials between PFPP and CBT for PD are clearly needed, Brewin and Bradley [44] have argued that RCTs comparing two or more treatments may give misleading results if patients’ preferences for the offered treatment alternatives are not controlled for. Thus, to the extent that patients’ preferences reflect their suitability for a specific type of psychotherapy, the one that is the most suitable for the majority of the patient population will appear superior, even if the treatments are equally effective. In a qualitative follow-up study of patients who had received CBT and PDT, patients who had unsuccessful treatment felt they had received a form of therapy that was less suitable to their individual needs and disposition and had well-developed ideas about how a more effective treatment should have been carried out [45]. A series of studies have shown that most people given adequate information will voice definite ideas about the kind of treatment that might be most suitable to their needs: so-called ‘helpfulness beliefs’ [46-48]. The resulting preferences are significantly moderated by the patient’s previous experiences with psychotherapy or psychiatry in general and generate a distribution of what may be a proxy for the ‘suitability differential’ between different forms of psychotherapy [48].

So, in a trial comparing two or more treatments where patients are allowed to select their preferred evidence-based treatment, one might reasonably predict little or no difference between the treatment groups. Also, if one assumes that outcome is at least partly moderated by the quality of the treatment alliance, one might reasonably expect stronger effects generally for treatments that were patient-selected than randomly assigned. It is possible to separate the effects of patient preference from the effects of randomization (that is treatment) by using a hybrid, double-randomization design [49]. In such a trial patients are randomized to self-selection or random assignment of treatment conditions.

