### Screening and baseline assessment

When a clinic identifies a potential participant, or when a participant directly contacts a member of the research team, an initial phone screening is carried out and the patient is informed about the trial, and inclusion and exclusion criteria are discussed. Patients who are currently receiving psychotherapy for PD or any other condition are strongly advised to complete their current course of treatment and then re-contact the team if they are still interested in participation. (At the time of writing, 138 patients have been enrolled in the trial. Of these, none were receiving ongoing psychotherapy for any condition at the time of screening. Only two patients who were receiving psychotherapy for PD expressed an interest in the trial and both were asked to complete their treatment before re-contacting the team and were not enrolled). Patients who are currently receiving medication for anxiety or any other psychiatric condition are advised to meet with their psychiatrist and to bring a copy of the trial information form to discuss participation and the trial criteria regarding medication before agreeing to further assessment for the trial.

Provided the patient has problems primarily of an anxious nature, wants treatment and does not meet any of the exclusion criteria, a face-to-face assessment is scheduled. Before this assessment the patient is provided with further information about the trial to read and a range of questionnaires to complete (described below). During the face-to-face assessment the patient undergoes a structured diagnostic interview with a member of the research team to establish that DSM-IV PD with or without Agoraphobia is the current and principal diagnosis, the Panic Disorder Severity Scale is administered, and lastly a structured diagnostic interview is carried out to assess DSM-IV Axis II Personality Disorders. If the patient has PD with or without Agoraphobia and no exclusion criteria are met, the patient gives written consent to participate and is then randomized. Patients who are excluded at any time during the baseline assessments are encouraged to contact their local GP and/or mental health clinic, and where requested/necessary a formal letter of referral is prepared by the trial assessor.

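### The tertiary aim classes therapeutic alliance as a moderator of the preference effect, although alliance forms after randomisation and is, on the protocol's own argument, a route from choice to outcome

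*Protocol article*

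**What the plan says.** All references are to the protocol article. Under Study aims and objectives, the primary aim concerns the effect of preference itself on the trial's endpoints: "The primary aim of the project is to investigate the extent to which patient’s preferences for treatment influences a broad range of primary and secondary" (the sentence goes on to list them). The tertiary aim follows: "A tertiary aim is to evaluate in a multivariate fashion, interactions between patient preference and other potential moderators of outcome". Its examples are gender and age, then "symptom severity, Axis I and II comorbidity, medication use, strength of the therapeutic alliance, and therapist effects". The next sentence sets a separate aim: "Finally we aim to evaluate putative mechanisms of change associated with each of the evaluated treatments". The examples there are cognitive and behavioral change and reflective capacity; alliance is not among them.

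Two other places bear on the point. Under Screening and baseline assessment, once eligibility is established, "the patient gives written consent to participate and is then randomized"; therapy comes later. The Background opens its argument with a condition, "if one assumes that outcome is at least partly moderated by the quality of the treatment alliance", and draws from it the expectation that "one might reasonably expect stronger effects generally for treatments that were patient-selected than randomly assigned".

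**The concern.** A moderator of a randomised contrast should be fixed before randomisation, so that patients at a given level of it are comparable between conditions. Gender, age and baseline severity meet that condition. Alliance with the study therapist does not, because there is no therapist relationship when the patient is randomised.

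The Background makes this more than a question of vocabulary. It uses the language of moderation, but the step from alliance to better results under self-selection works only if choice improves alliance and alliance improves outcome. That is a mediating path.

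A model containing assignment, alliance and their product therefore conditions on a consequence of the randomised factor. Two things follow:

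- The assignment coefficient loses whatever part of the effect runs through alliance. It is also biased as a direct effect if something unmeasured influences both alliance and outcome.
- The product term compares patients with high alliance after choosing with patients with high alliance after being assigned. These may be different kinds of patient, so a difference between them is not evidence that alliance modifies the benefit of choice.

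At stake is a report that preference adds little once alliance is considered, when alliance may be how preference works.

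**Working it through.** **Anchor.** Power/sample size calculations assumes d = 0.4 for self-selection against random assignment and states 200 patients at alpha 0.05 and power 0.80. The two-group formula, with a two-sided test assumed, gives 2 × (1.960 + 0.842)² / 0.4² = 98.1, so 99 per condition and 198 in total. This agrees with 200. It is the simple main-effect formula; the two-level interaction calculation behind the protocol's figure was not reproduced. No error in that figure is claimed here. It only fixes the size of the total preference effect at 0.40.

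**Model.** Let A = 1 for self-selection and 0 for random assignment, M = alliance (variance 1 within condition), U = an unmeasured cause of both alliance and outcome, and Y = outcome.

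- M = aA + uU + error
- Y = cA + bM + gU + error, with c = 0.40 − ab so that the total effect is 0.40

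The protocol gives no values for a, b, u or g. All are assumptions, shown as a range. There is no true A × M interaction.

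**Coefficient of A.** In a regression of Y on A, centred M and A × M, the slope on M is b + ug, so the coefficient of A is 0.40 − a(b + ug). The true direct effect is 0.40 − ab.

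| a | b | True direct effect | Coefficient, u = g = 0 | Coefficient, u = g = 0.4 |
|---|---|---|---|---|
| 0 | any | 0.40 | 0.40 | 0.40 |
| 0.2 | 0.2 | 0.36 | 0.40 − 0.2 × 0.20 = 0.36 | 0.40 − 0.2 × 0.36 = 0.33 |
| 0.3 | 0.3 | 0.31 | 0.40 − 0.3 × 0.30 = 0.31 | 0.40 − 0.3 × 0.46 = 0.26 |
| 0.5 | 0.5 | 0.15 | 0.40 − 0.5 × 0.50 = 0.15 | 0.40 − 0.5 × 0.66 = 0.07 |
| 0.8 | 0.5 | 0.00 | 0.40 − 0.8 × 0.50 = 0.00 | 0.40 − 0.8 × 0.66 = −0.13 |

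A simulation of 1,000,000 records per setting, fitted with the interaction term, agrees with every row to within 0.004. For the 0.3/0.3 row it gave 0.310 and 0.261. With alliance left out, every setting returned about 0.40.

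**Interaction.** When u is the same in both conditions, the fitted interaction is zero, as it should be. If the common cause bears more strongly on alliance in the self-selection condition (u = 0.5 against 0.2, with b = 0.3 and g = 0.4), the slopes on M are 0.3 + 0.4 × 0.5 = 0.50 and 0.3 + 0.4 × 0.2 = 0.38. Their difference of 0.12 is a spurious interaction; the simulation gave 0.118.

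**The case against.** The strongest reply is that the harmful model is inferred. The tertiary aim is one sentence with a list given as examples. It states no equation, and it does not say that the preference effect will be read from a model containing alliance. Such detail commonly sits in the full protocol or analysis plan, which are not at hand. This limits the consequence to a conditional one. It does not remove the point, which concerns a classification the article states rather than a detail it omits.

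A reader might go further and infer that the trial's main preference result would be removed or biased. The document does not support that. The planned comparison of the randomised and self-selection conditions is described as straightforward, and the model terms listed under Power/sample size calculations include no alliance term (the list is not presented as complete). The primary aim is also stated separately from the tertiary one. Nor does the Background make alliance the whole route: it says that outcome depends on it at least partly, and complete removal would need complete mediation.

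Three further objections stand in part:

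- Without a common cause, the reduced values are correct direct effects. They mislead only if reported as the total effect.
- The spurious interaction of 0.12 needs confounding that differs between conditions, for which the document gives no evidence. It shows what could happen, not what to expect.
- Whether the association of alliance with outcome differs between chosen and assigned treatment is a fair descriptive question. It is not a test of effect modification.

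**Conclusion.** The point holds for the tertiary model. Alliance is a post-randomisation variable that the protocol's own reasoning places on the path from choice to outcome, yet the tertiary aim groups it with baseline moderators. If the model is fitted as the aim reads, the preference coefficient is not the total effect: for a total of 0.40 it would be about 0.36 to 0.15 over assumed paths of 0.2/0.2 to 0.5/0.5, and about 0.33 to 0.07 over the same paths with the assumed common cause. It stays at 0.40 if choice does not change alliance. The preference-by-alliance interaction has no reading as effect modification.

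The direction rests on the Background's expectation that choice improves alliance and alliance improves outcome. The sizes rest on assumed paths. A primary contrast fitted without alliance is unaffected. This is a cheap improvement, not a threat to the main comparison.

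**What to change.** 1. Restrict the moderator model to variables measured before the first randomisation: gender, age, baseline severity, baseline Axis I and II comorbidity and baseline medication use. Therapist effects are a clustering matter outside this point.
2. Move alliance to the mechanisms aim. That aim now covers mechanisms of each treatment, so reword it to include mediation of choice versus random assignment. Use alliance ratings taken before the outcome they are meant to explain, and state the assumptions about confounding of alliance and outcome.
3. State that the total assignment effect is always estimated from a model without alliance. The mediation model will contain both terms; label any assignment coefficient from it as a direct effect.

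The cost is rewording the aim and the matching analysis text; no further patients are needed. The article gives no time for the alliance rating, so the investigators should confirm that one precedes the outcome assessment. The downside is that alliance is no longer reported as a moderator, and any difference in its association with outcome between chosen and assigned treatment becomes descriptive only.

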## Methods/Design

### Study design

PCT and PFPP will be compared under two conditions, one in which patients are randomized to either form of therapy, and one in which they are asked to choose between them after having duly informed themselves about the two alternatives. The design is in keeping with recommendations for preference trials described by Long *et al*. [49].

### Setting

The study is carried out in ten outpatient mental health clinics located in three regions of Southern Sweden: Skåne (including Lund, Malmö, Eslöv, Arlöv and Trelleborg), Halland (including Halmstad, Falkenberg and Varberg), Jönköping (including Värnamo) and Dalecarlia (including Dalarna). These clinics are state-funded and responsible for the care and treatment of all individuals within their catchment area. The clinics receive referrals from the GP (family doctor), social services, employers, and directly from patients. In some cities some patients may be offered a brief psychological treatment in what are termed ‘first-line’ services (usually located in the GP clinics). However, and in the majority of cases, the clinics participating in this study are the first-line service for patients with mental health problems including panic and other anxiety disorders, and particularly those with significant psychiatric comorbidity or impairment in functioning. PCT and PFPP are delivered by therapists employed in the same clinics where the patient would ordinarily be treated.

### Participant inclusion criteria

We aim to maximize the external validity of the study to the extent possible by making the inclusion criteria as least restrictive as possible. Inclusion criteria are the following:Aged between 18 and 70 yearsCurrent, principle diagnosis of DSM-IV PD with/without Agoraphobia and more specifically:Have experienced at least 1 panic attack per week during the 3 weeks preceding the start of treatment; orIf PD with Agoraphobia is the principal diagnosis and the patients actively avoids situations that cause them panic, then the patient must:Score ≥ 5 on an apprehension question about having a panic attack; orScore ≥ 4 on the Avoidance-Alone Subscale of the Mobility Inventory for Agoraphobia; orMeet DSM-IV PD criteria and *not* be more appropriately diagnosed as Agoraphobia without a history of PD;Not currently engaged in on-going psychotherapy treatments and willing to refrain from starting non-study treatments during the treatment phase of the trial (discussed further below under screening and baseline assessment)Medications, if used, must be held constant throughout the treatment phase of the study, and patients will only be accepted if they have been on a stable dose of standard anti-panic medication for at least 1 month and continue to meet criteria for a current diagnosis of PD with or without Agoraphobia; andAbility to complete the active treatment phase (not including follow-ups) within 16 weeks

### Participant exclusion criteria

Current substance abuse/dependence. Patients with a prior history of substance abuse/dependence must have been in remission for this condition for at least 12 months prior to entering trial treatment; orCurrent psychosis, delusions, or mania; orAcutely suicidal; orA history and current clinical presentation of at least one clinically-significant medical condition (for example, brain damage, degenerative neurological condition) sufficient to cause cognitive or physical impairments that might prevent full participation in treatments; orActive involvement in a legal dispute related to their mental health

### Recruitment procedure

This trial is carried out with significant support from regional health authorities and thus the primary means of recruitment is through state-funded, outpatient mental health clinics. Information about the study is posted in waiting rooms and all clinic staff are made aware of the study and asked to inform new referrals and existing patients who suffer from problems related to anxiety and panic specifically about the trial. Information about the trial is also available through a Project POSE website. Individuals with panic-related problems who visit the website are invited to contact the researchers for further information about the trial and an assessment of trial eligibility. Recruitment levels at the ten different sites are monitored on a monthly basis and problems addressed at the appropriate organizational level. Protocols governing inclusion have been developed and disseminated to facilitate a strict and coherent plan of action across sites, treatments conditions, therapists and site managers should problems arise.

### Screening and baseline assessment

When a clinic identifies a potential participant, or when a participant directly contacts a member of the research team, an initial phone screening is carried out and the patient is informed about the trial, and inclusion and exclusion criteria are discussed. Patients who are currently receiving psychotherapy for PD or any other condition are strongly advised to complete their current course of treatment and then re-contact the team if they are still interested in participation. (At the time of writing, 138 patients have been enrolled in the trial. Of these, none were receiving ongoing psychotherapy for any condition at the time of screening. Only two patients who were receiving psychotherapy for PD expressed an interest in the trial and both were asked to complete their treatment before re-contacting the team and were not enrolled). Patients who are currently receiving medication for anxiety or any other psychiatric condition are advised to meet with their psychiatrist and to bring a copy of the trial information form to discuss participation and the trial criteria regarding medication before agreeing to further assessment for the trial.

Provided the patient has problems primarily of an anxious nature, wants treatment and does not meet any of the exclusion criteria, a face-to-face assessment is scheduled. Before this assessment the patient is provided with further information about the trial to read and a range of questionnaires to complete (described below). During the face-to-face assessment the patient undergoes a structured diagnostic interview with a member of the research team to establish that DSM-IV PD with or without Agoraphobia is the current and principal diagnosis, the Panic Disorder Severity Scale is administered, and lastly a structured diagnostic interview is carried out to assess DSM-IV Axis II Personality Disorders. If the patient has PD with or without Agoraphobia and no exclusion criteria are met, the patient gives written consent to participate and is then randomized. Patients who are excluded at any time during the baseline assessments are encouraged to contact their local GP and/or mental health clinic, and where requested/necessary a formal letter of referral is prepared by the trial assessor.

### Inclusion measure

In keeping with the recommendations for standardized assessment of panic disordered patients described by Shear and Maser [54] and followed in most RCTs with panic disordered patients, inclusion is based on diagnostic status as assessed by the Structured Clinical Interview for DSM-IV (SCID-I) [55].

### Primary outcome measures

Panic Disorder Severity Scale [56]Panic Disorder Severity Scale-Self Report [57]Occupational statusPatient report of the total of number of absences from work due to sickness (and compensation for the same as part of the secondary, healthcare utilization outcome)

The above outcome measures are all assessed at baseline, post-treatment and 6-, 12- and 24-month follow-ups. The total of number of absences from work due to sickness at baseline is measured as including the 3 months prior to commencing treatment.

### Secondary outcome measures

Psychiatric comorbidity as assessed by the Structured Clinical Interview for DSM-IV Axis I diagnoses [55] and Structured Clinical Interview for DSM-IV Axis II diagnoses [58]Mobility Inventory for Agoraphobia [59]Montgomery Åsberg Depression Rating Scale [60]Sheehan Disability Scale [61]Clinical Outcomes in Routine Evaluation [62]Work Ability Index [63]Number of absences from work due to sickness before, during and after treatment as recorded in the Longitudinal Integration Database for Health Insurance and Social Studies (LISA) that is maintained by the Swedish Central Statistical OfficePatient report of healthcare utilization (for example, number of medical contacts, emergency room visits, prescription medication use)Use of psychotropic medication as recorded by the Swedish National Board of Health and Welfare register of consumption of psychotropic drugs; andEstimation of the total expected costs of each treatment alternative against the total expected benefits

### Randomization and allocation concealment

Randomization is done sequentially as patients are included in study. At the level of the clinic, there must be at least one PFPP and one PCT therapist working in the trial. The randomization procedure was designed to ensure equal numbers of patients in each condition at clinic level.

Because of the length of the follow-up (24 months) and the heavy assessment burden for patients throughout the trial, there is an increased risk of attrition during the follow-up period. To help minimize this risk, an effort is made to establish a good working relationship between a single trial assessor (who is not involved in delivering treatment) and each patient and to have the same assessor carry out the baseline, post-treatment and 6-, 12- and 24-month follow-up assessments. Because the baseline assessor reveals the randomization results to the patient, the post-treatment and follow-up interviews are not carried out blind to treatment condition. However all post-treatment and follow-up interviews are recorded and these interviews will be evaluated by independent raters who are blinded to treatment condition and these ratings will be reported.

